### Provisions for post-trial care {30}

This aspect is not relevant as there is no ancillary or post-trial care provided to the children.

### Outcomes {12}

The primary outcome variable is the mean plaque score change in children after 6 months assessed using the Oral Cleanliness Index [16]. The secondary outcomes are: (1) changes in the children’s oral health behaviours after 6 months, (2) mean change in parental OHL score after 6 months, and (3) qualitative data on the process evaluation of the SIMSP using the perspectives of DTs, teachers, and parents in terms of the appropriateness, effectiveness, facilitators, and barriers to the SIMSP implementation.

#### Dental caries status

Dental caries will be assessed using the International Caries Detection and Assessment System (ICDAS) [15] which allows for the detection and assessment of caries experience in children. Although caries is not one of the outcome measures, its assessment is taken as a proxy to show both groups are equal in terms of oral disease level at baseline.

#### Plaque score

Plaque score is assessed using the Oral Cleanliness Index which is a modification from the Silness and Loe Plaque Index for assessment of plaque [16]. Assessment for the presence of visible plaque will involve examining the labial surfaces of upper anterior teeth segments from upper right to upper left primary canines. Each surface is recorded using the following codes: 0—teeth appear clean, 1—presence of plaque around the labial cervical margins and covering less than ½ of labial tooth surface, 2—plaque covering more than ½ of labial tooth surfaces, and 9—assessment cannot be made.
b)Parents/guardians questionnaire

The questionnaire consists of 3 sections. Section A consists of items on the socio-demographic characteristics of parents (age, relationship with child, education level, total household income, and family status). Section B consists of items on child’s oral health-related behaviours (tooth brushing, use of fluoride toothpaste, bottle feeding, sugary food and drinks consumption, history of dental visit, and fluoride varnish application). Section C consists of the Malay version of Dental Health Literacy Assessment Instrument (Malay-DHLAI) [17] which consists of 3 parts: Oral Health Knowledge (OHK) domain (12 items), Comprehension domain (5 items), and Skills and Motivation (SM) domain (39 items). The OHK domain contains items on basic dental knowledge, knowledge on oral health promotion, oral health protection, disease prevention and dental visit. Each item is assessed by one correct answer from 4 answer options with total score ranged from 0 to 12. The Comprehension domain contains items on parents/guardians’ ability to understand healthcare instructions using their comprehension skill. Each item is scored by true/false answer options with total score ranged from 0 to 5. The SM domain assesses parents/guardians’ perceptions on their skills and motivation for child’s oral healthcare. Each item is assessed using a 5-point Likert scale (strongly disagree to strongly agree) with total score ranged from 0 to 39.

#### Qualitative data collection

FGD with DTs and teachers will be conducted separately to assess the implementation process of the SIMSP. The interview grid will be developed by identifying essential domains from the literature for evaluating the implementation process of the SIMPS’ protocol. The identified domains are ‘appropriateness’, ‘effectiveness’, ‘facilitators’, and ‘barriers’ to the implementation of the SIMSP. The domains will be included in the interview grid using semi structured open-ended questions to obtain participants’ feedback during FGD. The interview grid with the questions will be tested prior to its use in the study. An in-depth interview with parents will be conducted using the same interview grid. This method is suitable for parents as they have different work commitments. The FGD and in-depth interviews will be conducted by experts who are trained in qualitative methodology. Data collection is expected to last for 1.5 months. For FGD, all DTs and teachers will be included. For in-depth interview, data collection will continue until data saturation has been reached.

##### Sample size {14}

Sample size calculation is based on the effect of the SIMSP on plaque score reduction of the children compared to the POHP after 6 months with a small effect size dz. = 0.30, α = 0.05, power = 0.8. Using G*Power version 3.1.9.2 software, the total number of sample is *n* = 352 (176 per group). This number is increased by 20% to account for non-respondents [18], and multiplied by a design effect of 1.5 to produce the final sample size, *n* = [352 + (352*0.2)] × 1.5 = 634 (317 child per group).

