**Methods:**

This study is a pragmatic, cluster-randomised, parallel-group, matched pair, controlled trial with blinded outcome assessment. Randomisation is performed using a computer-generated table with a 1:1 allocation comparing the SIMSP and the POHP involving 28 preschools in the Kampar district, Perak, Malaysia. The intervention consists of preschool visits by a group of dental therapists, in-class oral health lessons and daily toothbrushing conducted by class teacher, child home toothbrushing supervised by parents, and infographic oral health messages to parents. The control consists of the existing POHP that involves preschool visits by a group of dental therapists only. The trial lasts for 6 months. Primary outcome variable is the mean plaque score change after 6 months. To determine the feasibility of the SIMSP, a process evaluation will be conducted using the perspectives of dental therapists, teachers, and parents on the appropriateness, effectiveness, facilitators, and barriers to the SIMSP implementation as well as an audit trail to assess the trial intervention.

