### Assignment of interventions: allocation

#### Sequence generation {16a}

The 53 preschools in the Kampar district are paired according to geographical location and preschool characteristics into 24 pairs (5 preschools are not paired as their locations are far away from each other). In this study, a two-stage randomisation of preschools will be applied. In the first stage, 14 pairs of preschools are randomly selected using computer generated table. In the second stage, using similar method, preschools in each pair will be randomly allocated into intervention and control group with a 1:1 allocation.

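### The 80% power stated for 634 children is slightly overstated once the planned loss occurs: mislabelled effect size, ×1.2 inflation for loss, and child-level degrees of freedom for 28 preschools

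*Protocol article*

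**What the plan says.** The Protocol article, Sample size {14}, works "with a small effect size dz. = 0.30, α = 0.05, power = 0.8" in G*Power and obtains a total of "352 (176 per group"). It then says "This number is increased by 20% to account for non-respondents [18], and multiplied by a design effect of 1.5". The printed formula is ["352 + (352*0.2)] × 1.5 = 634 (317 child per group").

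The number of randomised units is fixed elsewhere. The abstract's Methods paragraph describes the comparison as "involving 28 preschools in the Kampar district, Perak, Malaysia". Sequence generation {16a} says "In the first stage, 14 pairs of preschools are randomly selected using computer generated table", followed by 1:1 allocation within each pair. Statistical methods {20a} names the preschool as the unit of randomisation and the child as the unit of analysis, with cluster effects to be addressed. Trial status refers to multi-level analysis.

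**The concern.** The section prints a complete calculation, so it can be checked step by step, and three steps do not fit the design.

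- **Label.** dz is the standardised effect for paired differences. The trial compares two groups, and 176 per group is a two-group answer.
- **Loss.** Adding 20% to the number needed and then losing 20% of the enlarged number leaves fewer than were needed.
- **Degrees of freedom.** A design effect inflates the variance. It does not change the t reference distribution, which with 14 preschools per arm should reflect the number of clusters, not the number of children.

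At stake is how the result is read. Under Scientific hypothesis, the programme may replace the existing one if it proves effective. A null result would be judged against a stated 80% power that the design may fall somewhat short of.

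**Working it through.** **Inputs from the protocol.** Effect size 0.30, α = 0.05, power 0.80, 352 children, ×1.2, design effect 1.5, 634 children (Sample size {14}); 28 preschools (abstract); 14 pairs (Sequence generation {16a}).

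**Assumptions.** The test is two-sided; the section does not say so, but only two-sided testing reproduces 352 (one-sided gives 139 per group). Preschools are of equal size. No gain is credited for matching or baseline adjustment.

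**1. Reproduce the plan's figures.** An independent two-group t-test with d = 0.30, two-sided 0.05, needs 176 per group, 352 in total, with 350 df and power 80.1%. Then 352 × 1.2 × 1.5 = 633.6, rounded to 634. Both figures reproduce.

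**2. Check the label.** A two-sided paired t-test with dz = 0.30 needs 90 pairs (power 80.4%). So 352 follows from d, not from dz.

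**3. Check the loss step.**
- Children left after 20% loss: 634 × 0.8 = 507.2.
- Effective number at design effect 1.5: 507.2 / 1.5 = 338.1, against 352 needed.
- Matching enrolment: 352 × 1.5 / 0.8 = 660, which is 26 more than 634.

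**4. Power after 20% loss.** The noncentrality parameter is d × √(effective n per arm / 2). The degrees of freedom are 28 − 2 = 26 if pairs are ignored and 14 − 1 = 13 if pairs are respected.

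*Reading A, design effect stays at 1.5.* Effective n per arm is 338.1 / 2 = 169.1, and the noncentrality is 0.30 × √(169.1 / 2) = 2.76.

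*Reading B, 1.5 belongs to the enrolled cluster size.* Using design effect = 1 + (m − 1) × ICC:
- Enrolled m = 634 / 28 = 22.64, so the implied ICC = 0.5 / 21.64 = 0.0231.
- Retained m = 22.64 × 0.8 = 18.11, so the design effect = 1 + 17.11 × 0.0231 = 1.395.
- Effective n per arm = 507.2 / 1.395 / 2 = 181.7, and the noncentrality is 0.30 × √(181.7 / 2) = 2.86.

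| Scenario | Child-level df | 26 df | 13 df |
|---|---|---|---|
| A: 20% loss, design effect 1.5 | 78.5% | 75.7% | 72.3% |
| B: 20% loss, design effect about 1.40 | 81.4% | 78.6% | 75.3% |
| No loss, 634 analysed, design effect 1.5 | 86.8% | 84.3% | 81.3% |

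**5. Effect detectable with 80% power after 20% loss.** Reading A gives d = 0.32 (26 df) or 0.33 (13 df). Reading B gives 0.31 or 0.32.

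**6. If 20% is only an inflation factor.** The factor 1.2 matches a loss of 1 − 1/1.2 = 16.7%, leaving 528 children. At design effect 1.5, power is 77.3% (26 df) or 74.0% (13 df). With the design effect recomputed at 528 / 28 = 18.86 children per preschool (about 1.41), it is 79.7% or 76.4%.

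**The case against.** Most of the defence bears on the size of the shortfall, and much of it stands.

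- **The loss step is a small matter by itself.** On child-level degrees of freedom it gives 78.5% under reading A and 81.4% under reading B. The section gives an inflation of 20%, not an attrition rate, and with a 16.7% loss power on 26 df can reach 79.7%. This stands.
- **The degrees of freedom are not an input the protocol states.** A design-effect calculation is a common approximation, and no pair-level test on 13 df is specified. This stands as to 13 df. It does not remove the point that 350 df cannot describe a comparison of 28 randomised preschools.
- **The 13-df figures charge for matching without crediting it.** If the variance of the difference is multiplied by 1 − r, a pair correlation of preschool means of about 0.17 restores 80% under reading A, and about 0.11 under reading B. Pairs are formed on location and preschool characteristics, so some correlation is plausible. This stands; the protocol quantifies none.
- **The label changes no number.** True: the two-group meaning is clear from the context. The text as printed still does not lead to 352.

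A reader might also infer that the lack of an ICC behind the 1.5 is an error, or that a table of power against ICC is owed. The document does not support that. It is a condensed article, and such detail may sit in the full protocol. The implied ICC above is used only to show how the design effect moves with cluster size.

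**Conclusion.** The point holds in a limited form. Sample size {14} mislabels the effect size, uses a multiplier that does not offset a 20% loss, and takes its t reference from children when preschools are randomised. With 20% loss and no credit for matching or baseline adjustment, 634 children in 28 preschools give about 76–79% power on 26 df and 72–75% on 13 df, a shortfall of about 1 to 8 points from 80%. The cluster degrees of freedom account for most of it.

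A reader might conclude that power is simply 72–76%, or that the trial is seriously underpowered. The protocol does not support either. That narrower range fixes the design effect at 1.5 after clusters have shrunk. The shortfall also needs the loss to occur: with all 634 analysed, power is 84% or 81%. The detectable effect rises from 0.30 to at most about 0.33, and no estimate, interval or test changes. This is a minor to moderate correction.

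**What to change.** Reword the one paragraph in Sample size {14}:

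- Call the effect size d, the between-group difference in standard deviations of plaque change, in place of dz.
- Either give 660 as the enrolment matching a 20% loss (352 × 1.5 / 0.8), or keep 634 and say what it delivers after that loss.
- Restate power on cluster-level degrees of freedom as about 72–79% after 20% loss (detectable d up to about 0.32–0.33). Name the two assumptions behind the range: 26 or 13 df, and design effect 1.5 or about 1.40. Add that pair correlation or baseline adjustment may recover part of the shortfall.

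No extra children are proposed. Trial status reports that recruitment ended in April 2019 and the primary outcome was collected in October 2019. The cost is a few sentences and a slightly less favourable stated power.

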##### Recruitment {15}

The study sample consists of children who attend preschools on weekdays. As a result, enrolment of eligible children will not pose a problem provided parental consent is obtained.

### Assignment of interventions: allocation

#### Sequence generation {16a}

The 53 preschools in the Kampar district are paired according to geographical location and preschool characteristics into 24 pairs (5 preschools are not paired as their locations are far away from each other). In this study, a two-stage randomisation of preschools will be applied. In the first stage, 14 pairs of preschools are randomly selected using computer generated table. In the second stage, using similar method, preschools in each pair will be randomly allocated into intervention and control group with a 1:1 allocation.

#### Concealment mechanism {16b}

The allocation concealment is achieved by having a senior dental officer in the Kampar district who is not involved in the study to keep the allocation sequence in a brown envelope. The information will be kept safe until the preschool pairs have been recruited into the study.

#### Implementation {16c}

The allocation sequence of the preschools will be generated by the statistician employed at the Faculty of Dentistry, University of Malaya using computer-generated table. The information will be kept confidential until the interventions are assigned to the preschools. The children in the preschools will be enrolled by the DT team who will be in charge of implementing the intervention.

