### Who will take informed consent? {26a}

DTs will inform parents about the study in a letter to be sent through school teacher. The letter contains information sheets about the study and a consent form. A contact telephone number is included in the consent form for parents to call the DTs if they have any questions about the study. A written informed consent from parents will be obtained before their child can be included in the study.

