#### Phase 1: DT first visit to preschools in both groups

A written informed consent from parents for their children’s involvement in trial will be sought when the preschools open in the new academic year. The first visit of DTs to preschools occurs in the beginning of the year to conduct an oral examination of the children for caries and dental plaque. In the SIMSP group, the presence of crowding/deep fissures on the teeth will be charted and this information will be included in the CRA form. A self-administered questionnaire for parents will be sent through class teacher.

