### Trial status

Recruitment of preschools was completed in February 2019 and recruitment of children was completed by April 2019. The primary outcome variable at 6-month follow-up was collected in October 2019. The quantitative data of the secondary outcome variables were collected in November 2019. Qualitative data collection for the secondary outcome variables is still ongoing; the FGD and in-depth interviews were stopped in February 2020 due to the movement control order enforced by the government in response to the Covid-19 pandemic, and are expected to resume in August 2020. Online FGD and in-depth interviews are not feasible as many parents and teachers in Kampar district do not have access to internet connection at home. Quantitative data entry and cleaning have been completed but multi-level data analysis is still ongoing due to the Covid-19 pandemic. The results of the trial are expected to be released to the stakeholders when all the analysis of the primary and secondary outcome variables have been completed.

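### Concealment as described protects the selection of preschools only; whether the arm was hidden while children were enrolled is not stated, so consent that differs by arm is an open risk

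*Protocol article*

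**What the plan says.** All references are to the protocol article.

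- **Release of the allocation.** Concealment mechanism {16b}: "The information will be kept safe until the preschool pairs have been recruited into the study". Implementation {16c} gives a second end point: "The information will be kept confidential until the interventions are assigned to the preschools". Neither is tied to parental consent.
- **Who enrols.** Implementation {16c}: "The children in the preschools will be enrolled by the DT team who will be in charge of implementing the intervention".
- **How consent is sought.** Who will take informed consent? {26a}: "DTs will inform parents about the study in a letter to be sent through school teacher", and "A contact telephone number is included in the consent form for parents to call the DTs if they have any questions about the study". Written consent is required before a child is included.
- **When consent is sought.** Phase 1: "A written informed consent from parents for their children’s involvement in trial will be sought when the preschools open in the new academic year".
- **What happens at the first visit.** Same section: "In the SIMSP group, the presence of crowding/deep fissures on the teeth will be charted". The result goes into the caries risk assessment form.
- **Actual dates.** Trial status: "Recruitment of preschools was completed in February 2019 and recruitment of children was completed by April 2019".
- **Who is blinded.** Who will be blinded {17a} names the examiners, and the data monitoring section {21a} adds the data-entry person. Those who enrol children are not mentioned.
- **Acknowledgement.** The abstract's discussion names cluster selection bias and says it will be dealt with in analysis and interpretation.

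**The concern.** In a cluster trial two selections matter: which clusters enter and which individuals within them enter. The sealed envelope addresses the first. The second depends on whether the people inviting families, and the families themselves, know the arm at the time.

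That is a substantive question here, because the arms ask different things of parents. Under Intervention description {11a}, SIMSP parents attend a meeting, receive fortnightly messages and supervise brushing at night; POHP parents do none of this. The main Discussion section itself calls parents' willingness to monitor home brushing a challenge. Willingness is plausibly related to how a child's plaque changes. If it affects consent in one arm more than in the other, the consenting children differ between arms before any programme effect.

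The planned protections do not repair this. Allowing for cluster effects corrects the variance. Intention-to-treat starts from the children enrolled and cannot recover families who declined. Blinded examination protects measurement. At stake is the reading of the primary outcome, on which the Scientific hypothesis section rests the possible replacement of POHP by SIMSP.

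**Working it through.** **1. Order of events**

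| Evidence | What it shows | What it does not show |
|---|---|---|
| {16b}: kept until pairs are recruited | A minimum holding period, ended by preschool recruitment | That the arm was released at that moment |
| {16c}: confidential until assignment | Release is tied to assignment, not to consent | The date of assignment |
| Phase 1: SIMSP-only charting | The arm is known to field staff at the baseline visit | That it was known when consent was asked; consent precedes a child's inclusion |
| Phase 2: intervention starts two weeks after the first visit | Assignment after consent would have been possible | That it happened; the Phase 1 charting points the other way for the baseline visit |
| Trial status: preschools February 2019, children by April 2019 | Child recruitment finished no earlier than preschool recruitment | Whether any consent was sought after disclosure |

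No step hides the arm from those enrolling children, and no statement says that it was known to them.

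**2. The plan's own effect size, used as the scale**

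Sample size {14} gives 0.30, α = 0.05, power 0.8 and a total of 352. A two-sided independent two-sample t-test with these inputs needs 175.4, so 176 per group and 352 in total. Then 352 × 1.2 × 1.5 = 633.6, rounded to 634. Both figures reproduce. The effect is labelled dz, but the total is that of two independent groups, so 0.30 serves here as a between-arm difference in SD units.

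**3. Illustration A (all inputs assumed)**

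Let c be the consent rate, and let non-consenters have a plaque change d SD worse than consenters, with the same d in both arms. Consenters then exceed all eligible children by d × (1 − c), and the spurious difference between arms is

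bias = d × [(1 − c_SIMSP) − (1 − c_POHP)].

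With d = 0.5, c_SIMSP = 0.70 and c_POHP = 0.85: 0.5 × (0.30 − 0.15) = 0.075 SD, and 0.075 / 0.30 = 25% of the planned effect. Exchanging the two consent rates gives −0.075 SD.

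**4. Illustration B (all inputs assumed)**

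Half of families are motivated, and their children's plaque change is better by g SD. Consent is 80% throughout, except among less motivated SIMSP families, where it is u. The motivated share of SIMSP consenters is 0.8 / (0.8 + u), against 0.5 in control, so bias = g × [0.8 / (0.8 + u) − 0.5].

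| u | Motivated share, SIMSP | Bias, g = 0.3 | Bias, g = 0.5 | Share of 0.30 |
|---|---|---|---|---|
| 0.80 | 0.500 | 0 | 0 | 0% |
| 0.70 | 0.533 | 0.010 | 0.017 | 3–6% |
| 0.60 | 0.571 | 0.021 | 0.036 | 7–12% |
| 0.50 | 0.615 | 0.035 | 0.058 | 12–19% |

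In both illustrations the bias is zero when consent is equal in level and type. The number of children does not enter either formula, so a larger sample would not shrink it.

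**The case against.** The strongest reply is that the order is inferred. No section dates the randomisation or says that therapists or teachers knew the arm when they approached parents. A reader might conclude from the February and April dates that children were enrolled after disclosure. Those dates fix only when each recruitment ended. The SIMSP-only charting is the firmest evidence, and it concerns the baseline examination, which follows consent. This objection stands and limits the point to an unprotected step.

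Second, the route is narrow. Consent is by letter through the teacher, therapists speak with parents only if parents telephone, and no arm-specific letter is described. A reader might also infer that the enrolling team has a stake in SIMSP alone, but dental therapists deliver the control programme too, and no separate SIMSP team is described. This lessens the concern without removing it: the letter passes through the teacher, who in SIMSP carries out the lessons and daily brushing, and nothing says that the teacher was unaware of the arm.

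Third, direction is uncertain. The extra demands could lower SIMSP consent; the free toothbrush and toothpaste could raise it. This stands, so the illustrations must be read with either sign.

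Fourth, the article acknowledges cluster selection bias and collects baseline plaque, caries and family characteristics. These are useful materials, but the consent, concealment and implementation sections contain no safeguard at the consent stage, and caries is justified only as a proxy to show that the groups are equal at baseline.

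**Conclusion.** The point holds as an open risk. As written, concealment reaches the preschools and stops there. The implementing team enrols the children, an arm-specific step at the first visit implies that the arm is known by baseline, and the documents do not say whether disclosure came before or after parental consent.

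The documents do not support the stronger statement that consent did differ by arm, or that the result is biased. Size and direction are unknown. The range of 0 to about 0.075 SD in either direction, at most a quarter of the planned 0.30, rests wholly on assumed consent rates and assumed differences between families. It shows that the issue could matter and is not an estimate. What the gap does affect is interpretation: without consent figures by arm, a programme effect cannot be cleanly separated from a difference in who agreed to take part.

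**What to change.** Trial status reports recruitment closed and the multilevel analysis still under way. A later opening of the envelopes can no longer be introduced, and the text should not be reworded as if it had been done. What remains:

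1. Adjust the primary multilevel model for baseline plaque and baseline caries, recording this choice before the arms are compared. Both are already collected. This reduces selection related to those measures but not selection on unmeasured parental motivation.
2. Report the numbers of children eligible, approached and consented, per preschool and per arm.
3. State when the arm became known to the dental therapists and to the teachers, relative to parental consent.
4. Describe concealment as preschool-level only, and name recruitment bias as a limitation on the conclusion.

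The cost is two covariates in a model not yet final, one flow table, and a few sentences in {16b} and {16c} and in the trial report. If records of children approached were not kept, that should be said.

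For a future trial of this design, open each pair's envelope only after consent and the baseline examination are complete in both preschools. The two weeks between the first and second visits leave room for this. The crowding and fissure charting would then have to be done in both arms or moved to the second visit, since a SIMSP-only step at the first visit would defeat the arrangement.
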